## Abstract

**Background:**

The therapeutic window within which induced hypothermia might be effective after cardiac arrest is still unknown. In animal cardiac arrest models, early induction and faster cooling are independently associated favorable outcome. However, induction of Ultra-Rapid Therapeutic Hypothermia (achieving core body temperature of 33.0 ± 0.5 °C within 60 min after the start of the procedure) still need to be evaluated in the human setting. Total liquid ventilation with temperature-controlled breathable liquids provided such rapid cooling (i.e. >15 °C/h cooling rate) in both small and large animals. This method was shown to improve neurological outcome in animals. A new medical device system, Vent2Cool, was developed for clinical use in the Intensive Care Unit to achieve ultra-rapid therapeutic hypothermia by total liquid ventilation to patients.

**Materials and methods:**

The non-blinded and single-arm OverCool pilot trial will evaluate the feasibility, cooling performance and safety of ultra-rapid therapeutic hypothermia by total liquid ventilation in 24 patients resuscitated after in- or out-of-hospital cardiac arrest. Inclusion criteria will include presumption to start ultra-rapid cooling procedure in the Intensive Care Unit within less than 120 min after resuscitation. The primary outcome will be the achievement of a core temperature of 33.0 ± 0.5 °C, as well as successful return to conventional gas ventilation within <60 min after procedure initiation. Secondary outcomes will include time to reach target temperature, vital status, systemic and pulmonary parameters and modified-Rankin Score at 28 days post- cardiac arrest.

**Conclusion:**

The OverCool study is a pilot study to validate performance and safety of ultra-rapid therapeutic hypothermia using total liquid ventilation for resuscitated cardiac arrest patients.

**Registration and authorization:**

NCT06798818. Authorized by the French “Agence nationale de sécurité du médicament et des produits de santé” and “Comité de Protection des Personnes” (Ethics Committee).

## Introduction

“Targeted Temperature Management (TTM)” within the hypothermic range of 32–34 °C, commonly referred as therapeutic hypothermia, has been proposed as an intervention to attenuate post-cardiac arrest syndrome (PCAS) in patients successfully resuscitated following out-of-hospital cardiac arrest (OHCA).^1^, ^2^ Following promising pilot studies in the early 2000 s, large-scale clinical trials have demonstrated that TTM at 33 °C with existing techniques does not significantly improve outcomes compared to sub-normothermia (36 °C)^3^ or strict normothermia (37 °C)^4^ after resuscitation. Current guidelines recommend to provide controlled normothermia in CA survivors,^5^ while whether therapeutic hypothermia might still benefit for some subgroup of patients remains unknown.^5^, ^6^

In contrast to the findings of most clinical trials, experimental studies frequently demonstrate that therapeutic hypothermia significantly improves neurological outcomes in animal models of cardiac arrest.^7^, ^8^ A recent meta-analysis of animal studies highlighted that the neurological benefits of hypothermia were independently associated with “faster cooling rates, lower target temperature of TTM within the range of 32–36 °C, and shorter duration of cooling”.^9^ Additionally, a recent Cochrane review, based on subgroup analyses, found that the beneficial effects of hypothermia were most pronounced when cooling was initiated within two hours of the return of spontaneous circulation (ROSC).^10^

A novel approach for achieving therapeutic hypothermia much faster than with traditional external or endo-vascular cooling systems is to perform total liquid ventilation (TLV) with cold breathable perfluorocarbon liquids, thereby using the lungs as thermal exchangers. This innovative technique has been shown in preclinical studies to rapidly lower core body temperature within minutes, providing significant neurological benefits across multiple animal models^11^, ^12^, ^13^, ^14^, ^15^, ^16^ while preserving normal gas exchange due to the unique properties of these breathable liquids. The method is engineered to achieve a target temperature of 33 °C in body core within one hour of initiation, irrespective of initial patient temperature. This is accomplished through a lung-conservative TLV strategy that precisely controls liquid pressure and maintains lung liquid volume below the functional residual capacity.

Here, we describe the design of a “first-in-human”, open-label, single-arm, non-comparative pilot clinical study, named **“***Lung-Conservative Liquid Ventilation for the Induction of Ultra-Rapid Cooling After Cardiac Arrest*” (OverCool), aiming at evaluating the performance and safety of ultra-rapid therapeutic hypothermia (URTH) induction by TLV.

## Methods

OverCool is an open-label, two-center, pilot study prospectively registered as NCT06798818 and authorized by the French authorities (Agence nationale de sécurité du médicament et des produits de santé) and Ethics Committee (Comité de Protection des Personnes). The trial is planned to recruit across Cochin Hospital (Assistance-Publique Hôpitaux de Paris, Paris, France) and Angers Hospital (CHU Angers, Angers, France). The protocol was developed by the trial investigators in accordance with national legislation, Good Clinical Practice and declaration of Helsinki. The trial is sponsored by ORIXHA, developer of the Vent2Cool system, and supervised and monitored by a Contract Research Organization (Clinact- MultiHealth, Velizy, France). The protocol manuscript was written in concordance with the SPIRIT guidelines. Additional information is provided in the Supplementary material.

### Trial objectives

The primary objective is to demonstrate the ability of the Vent2Cool medical system (Orixha, Paris, France) to perform hypothermic TLV. Vent2Cool performance and efficacy have been rigorously validated *in vitro* and *in vivo*.^11^, ^12^, ^13^, ^14^, ^15^, ^16^ URTH targeted the achievement of core body temperature of 33.0 ± 0.5 °C within 60 min after the start of the procedure in patients resuscitated after intra- or extra-hospital cardiac arrest.

As secondary objectives, the study will aim at demonstrating: the safety of the procedure, the cooling performance, the ability to be implemented in the emergency setting of post-cardiac arrest management, clinical outcomes and impact on biological markers.

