### Sample size and statistical analysis

The analyses will be conducted on the following patient sets: Safety population (SAF), Full Analysis Set (FAS) and Population Per Protocol (PP). The SAF includes all included and patients treated by Vent2Cool. The FAS (according to the Intent-to-Treat (ITT) principle) includes all treated patients, who had one post-baseline evaluation. The PP population includes all patients of the FAS except those with any major protocol deviation, that might significantly affect the completeness, accuracy, and/or reliability of the study data. The main endpoint analysis and secondary endpoint analyses will be based on the Full Analysis Set. A supportive analysis will be based on the Per Protocol population if more than 10% of patients are excluded from FAS.

A summary table and a flow chart will be presented for each patient population presenting the number of patients at each assessment and identifying the number of patients who withdrew over time, with the reason of premature study termination. Patients may withdraw from the study at any time, with or without reason and without prejudice to further treatment. Data that have already been collected on prematurely withdrawn patients will be retained and used for analysis, but no new data will be collected after withdrawal. Patients lost to follow-up, after hospital discharge before the end of the study, will be replaced. Data collected until the last available visit of these patients will be analyzed.

Based on an estimated success rate of around 80%, a sample of 24 analyzable patients was calculated as required to achieve sufficient precision of the success rate using Wilson's score interval, with a 95% confidence interval. Specifically, 19 of the 24 patients will have to undergo the procedure successfully, giving an expected success rate of 79.2% (95% CI [59.5%; 90.8%]).

Quantitative parameters will be described using the following summary descriptive statistics: number of patients, mean, standard deviation, median, first and third quartiles, and minimum and maximum values. Mean and standard deviation values will be reported to one decimal place greater than the data were collected. Median, first and third quartiles, minimum and maximum values will be reported with the same precision, as they were collected. Qualitative parameters will be described using frequencies and percentages.

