A hybrid method was then proposed through lung filling with the perflubron as breathable liquid followed by superimposing gas tidal volumes, known as partial liquid ventilation (PLV). Hirschl et al. evaluated this PLV method in 19 patients, including adults, children, and neonates, all of whom were also treated by extracorporeal membrane of oxygenation (ECMO) as a backup for gas exchange. Improvements in alveolar-arterial oxygen gradients and static lung compliance were documented during PLV under these conditions.^21^ A multicenter trial then examined the safety and effectiveness of PLV in about 300 patients using two different targets for lung filling, corresponding to approximately 10 or 20 ml/kg.^22^ The study showed no improvement in ventilator-free days or 28-day all-cause mortality and increased risk of pneumothorax with PLV, halting further research for presumed safety concerns. The risk of pneumothorax was known prior to this study^21^ and linked to the risk of overdistension when gas entered lung areas not fully filled with liquid, highlighting the need for pressure-controlled ventilation. Unfortunately, this PLV pivotal inadequately utilized volume-controlled gas ventilation with tidal volumes averaging 9 mL/kg, which is considered harmful even in conventional ventilation. In addition, the study’s design required fluctuating PEEP for regular lung refilling to compensate for evaporative loss with no possibility to control actual lung liquid volume. This could easily explain the failure of PLV in this study. Accordingly, alternative approaches like TLV may provide the expected benefits of liquid ventilation in a safer manner^20^, ^23^. For instance, the “lung-conservative liquid ventilation” approach was proposed for short-term TLV and URTH induction, through lung liquid volume reliably maintained below functional residual capacity. If the OverCool trial confirms TLV safety after cardiac arrest, it could reignite interest in liquid ventilation as a supplemental or alternative treatment for respiratory distress, advancing care beyond current gas ventilation practices.

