## Conclusions

The OverCool trial aims at demonstrating the performance and safety of URTH by TLV in resuscitated patients after cardiac arrest with the Vent2Cool system. Vent2Cool can be an innovative efficient approach to induce therapeutic hypothermia within 3 h after cardiac arrest. Its benefits on cardiac arrest clinical outcomes will need to be further investigated in comparative clinical studies. The OverCool trial can also pave the way for other applications of TLV in the ICU.

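### The article aims to demonstrate safety, but 24 uncontrolled patients sized on the procedure success rate can only describe it: even 0/24 events leaves a true rate of up to about 14% open

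*Protocol article*

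**What the plan says.** Four places in the protocol article set or foresee a firm safety conclusion:

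- Trial objectives: "As secondary objectives, the study will aim at demonstrating: the safety of the procedure".
- Abstract, Conclusion: "The OverCool study is a pilot study to validate performance and safety of ultra-rapid therapeutic hypothermia using total liquid ventilation".
- Conclusions: "The OverCool trial aims at demonstrating the performance and safety of URTH by TLV".
- Discussion, as a condition for wider interest in liquid ventilation: "If the OverCool trial confirms TLV safety after cardiac arrest".

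Two places are softer. The Introduction describes a first-in-human pilot "aiming at evaluating the performance and safety of ultra-rapid therapeutic hypothermia (URTH) induction by TLV", and the Materials and methods part of the abstract also speaks of evaluating.

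Under Sample size and statistical analysis, 24 analyzable patients are justified by the precision of a success rate of around 80%, with a Wilson 95% interval shown for 19 of 24. For categorical endpoints the section says: "Qualitative parameters will be described using frequencies and percentages". Continuous measures get summary statistics. Table 1 defines events for the individual patient, such as SpO2 below 75% for at least 5 minutes or systolic pressure below 60 mmHg. It gives no rate across patients against which the results would be judged.

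The same section defines a Safety population (included and treated patients) and a Full Analysis Set (treated patients with one post-baseline evaluation). It bases the secondary endpoint analyses, which by label include the secondary safety endpoints, on the Full Analysis Set.

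**The concern.** The aim and the design do not match. Demonstrating safety means showing that the rate of a relevant harm lies below some level, or is no worse than under a comparator. The article has no comparator, states no level, and did not size the trial on any safety quantity. What it states for binary harms is a count and a percentage. At this sample size a reassuring percentage can sit beside a substantial true rate.

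The conclusion would be used. The Discussion links confirmed safety to renewed interest in liquid ventilation for respiratory distress. It also recalls a trial of partial liquid ventilation in about 300 patients that showed an increased pneumothorax risk and halted further research. Against that history, what 24 patients can exclude should be written down before the results are known.

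**Working it through.** **Inputs.** From Sample size and statistical analysis: n = 24, expected 19 successes, two-sided 95% Wilson score interval. From Table 1: binary safety events, and a CT endpoint limited to Day 28 survivors. Assumptions, because the article gives no figures: true harm rates of 2%, 5% and 10%, and 8, 12 or 16 survivors.

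**Step 1: the plan's own figure.** Wilson limits are [p + z²/(2n) ± z√(p(1−p)/n + z²/(4n²))] / (1 + z²/n), with z = 1.96 and z² = 3.84.

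For 19/24, p = 0.792 and 1 + z²/n = 1.160. The centre is (0.792 + 0.080)/1.160 = 0.751 and the half-width is 0.156. The interval is 59.5% to 90.8%, exactly as stated.

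**Step 2: the same method for rare harms.** With no events the Wilson upper limit reduces to z²/(n + z²) = 3.84/27.84 = 13.8%. The Clopper-Pearson limit is 1 − 0.025^(1/24) = 14.2%. The one-sided 95% exact limit is 1 − 0.05^(1/24) = 11.7%.

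| Events in 24 | Wilson upper (two-sided 95%) | Clopper-Pearson upper (two-sided 95%) | Exact upper (one-sided 95%) |
|---|---|---|---|
| 0 | 13.8% | 14.2% | 11.7% |
| 1 | 20.2% | 21.1% | 18.3% |
| 2 | 25.8% | 27.0% | 24.0% |
| 3 | 31.0% | 32.4% | 29.2% |

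**Step 3: chance of never seeing a harm.** P(0 events) = (1 − p)^24.

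- p = 2%: 0.98^24 = 62%
- p = 5%: 0.95^24 = 29%
- p = 10%: 0.90^24 = 8%

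**Step 4: CT endpoint, no events, survivors only.**

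| Assumed survivors | Wilson upper | Clopper-Pearson upper |
|---|---|---|
| 8 | 32.4% | 36.9% |
| 12 | 24.2% | 26.5% |
| 16 | 19.4% | 20.6% |

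**Step 5: scale.** With no events, a one-sided 95% upper limit of at most 10% needs ln(0.05)/ln(0.90) = 28.4, so 29 patients. A limit of at most 5% needs ln(0.05)/ln(0.95) = 58.4, so 59. These levels only illustrate scale; neither is proposed as an acceptable rate.

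**Step 6: analysis set.** The Full Analysis Set is the treated patients less any without a post-baseline evaluation. It can therefore only equal the Safety population or be smaller. A patient whose course ended before any post-baseline evaluation would leave the denominator of the safety endpoints. The article does not allow the number of such patients to be estimated, and it may be zero.

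**The case against.** The strongest reply is that this is openly a first-in-human pilot, that imprecision comes with it, and that the verb is used loosely. In Trial objectives the same verb also governs clinical outcomes and biological markers, and Table 2 puts a list of temperature measurements under a heading about demonstrating cooling performance. The Discussion sentence is conditional and is not an analysis rule. This stands as far as it goes: nothing shows that a confirmatory safety test was intended. It does not remove the mismatch, because the abstract and Conclusions point the same way and the softer wording elsewhere shows that the article is inconsistent.

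A second reply is that intervals for safety endpoints may be in the full protocol, the supplement or the analysis plan. That also stands. Their absence is shown only for this article, and describing endpoints by percentages does not rule intervals out. Yet no fuller plan can give 24 uncontrolled patients the ability to demonstrate safety.

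A third reply is that much of Table 1 is continuous (blood gases, pressures, compliance), and that safe return to gas ventilation is part of the primary endpoint, which does have an interval. This is correct. The point is confined to the binary safety events.

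A reader might go further and infer that few or no events will be taken as proof of safety. The article states no such rule. Nor does it describe any safety test, so the point is not about a non-significant result being taken as safety.

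**Conclusion.** The concern holds as a mismatch between the stated safety aim and what the design and stated analysis can deliver. With 24 patients and no events, a rate of up to about 14%, or one patient in seven, remains compatible with the data. With one event it is about 20% to 21%. The CT endpoint is weaker: about 19% to 32% (Wilson) if 8 to 16 patients survive, which is an assumed range.

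The limits for 24 assume that all 24 patients are evaluable for the endpoint. The 29% chance of missing a harm rests on an assumed true rate of 5%. The analysis-set point is one of definition, with no size that can be given.

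**What to change.** 1. In the abstract's Conclusion, Trial objectives, the Discussion and the Conclusions, restate the safety aim as evaluating or describing safety, in line with the Introduction and the abstract's Materials and methods.
2. In Sample size and statistical analysis, report each binary safety endpoint of Table 1 with a two-sided 95% Wilson interval on its actual denominator (survivors scanned, for the CT endpoint). Base any safety statement on the upper limit. Beside the sample size, state that 0/24 excludes only rates above about 14%.
3. Analyse the Table 1 safety endpoints on the Safety population, and amend the sentence that places all secondary endpoint analyses on the Full Analysis Set.

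The cost is wording changes and one more column in the safety tables, using a method the article already applies to the primary endpoint. No patients or data are added. The downside is a more modest safety claim.

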### Primary and secondary endpoints

The primary endpoint is the success of the procedure, defined as the ability to reach a body core temperature (bladder recommended) of 33.0 ± 0.5 °C and a safe return to conventional mechanical ventilation within less than one hour after Vent2Cool start. Start of the Vent2Cool procedure is defined as the opening of the Vent2Cool patient connector valve. Secondary endpoints are shown in Table 1, Table 2.

**Table 1 t0005:** Summary of the secondary safety endpoints.

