**Secondary safety endpoints**
• SaO_2_, PaO_2_ and PaCO_2_ at inclusion, 10 and 25 min after the start of Vent2Cool procedure and 1 h, 2 h, 12 h, 24 h, 48 h and 72 h after the end of procedure
• Occurrence of an episode of severe oxygen desaturation (SpO_2_ < 75%) on pulse oximeter lasting at least 5′ during the Vent2Cool procedure
• Occurrence of severe hypercapnia (PaCO_2_ > 75 mmHg); hyperoxemia (PaO_2_ > 400 mmHg); hypoxemia with PaO_2_ < 75 mmHg in arterial blood at t = 10 and 25 min after starting Vent2Cool procedure
• Occurrence of an episode of major systemic hypotension (invasive or non-invasive measurement) with systolic blood pressure < 60 mmHg during Vent2Cool procedure
• Heart rate measured from the EKG or blood pressure signal at 10 and 25 min after starting Vent2Cool procedure and at t = 1 h, 2 h, 12 h, 24 h, 48 h and 72 h after the procedure
• Systemic systolic and diastolic blood pressure at 10 and 25 min after starting Vent2Cool procedure and at t = 1 h, 2 h, 12 h, 24 h, 48 h and 72 h after the procedure
• Presence of arrhythmia or unexpected electrocardiographic abnormality
• Early termination of the Vent2Cool procedure before reaching a core target temperature below 33 ± 0.5 °C (failure of cooling induction)
• Number and percentage of patients for whom the core temperature has reached a value lower than 30 or 32 °C within 60 min after the start of the Vent2Cool procedure
• Adverse events related to Vent2Cool procedure, i.e., appearance of a perfluorothorax, unexpected cardiac arrhythmia or major hemodynamic instability, major hypoxemia during or immediately after the Vent2Cool procedure (i.e., during the first hour following the end of the procedure)
• Ventilatory parameters after the Vent2Cool procedure, i.e., measured values of positive end-expiratory pressure (PEEP), end-inspiratory pause pressure (Plateau pressure), driving pressure and static pulmonary compliance at t = 1 h, 2 h, 12 h, 24 h, 48 h and 72 h after the Vent2Cool procedure
• Occurrence of pulmonary infection in the ICU
• Presence or absence of pleural collection of perfluorocarbon in the lungs on thoracic computed tomography examination in patients surviving on Day 28 after cardiac arrest.

**Table 2 t0010:** Summary of the secondary endpoints for cooling performance, implementation in the care pathway, survival and neurological outcome, and clinical pathology.

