### Eligibility criteria

Eligible patients will be unconscious patients resuscitated after extra- or intra-hospital cardiac arrest and admitted to the Intensive Care Units (ICU). Cardiac arrest from presumed cardiac or asphyxial origin, regardless of the heart rate initially recorded, will be included. Patients must be aged between 18 and 84 years with an ideal body weight (IBW) comprised between 40 and 93 kgs. Inclusion and exclusion criteria are shown in Table 3.

**Table 3 t0015:** Summary of inclusion and exclusion criteria.

Inclusion criteria	Exclusion criteria
• Patient resuscitated after extra- or intra-hospital cardiac arrest, from presumed cardiac or asphyxial origin, regardless of the heart rate initially recorded.	• Conscious patient
• Age between 18 and 84 years old	• Patient Ideal Body Weight less than 40 kgs or more than 93 kgs
• Time between collapse and return of spontaneous circulation (ROSC) < 60 min	• Traumatic cardiac arrest, drowning, exsanguination or sepsis
• Presumption, at the time of inclusion, of a possibility of starting Vent2Cool within a period of less than 120 min after ROSC.	• Temperature at admission < 34.0 °C
• Unconscious (GCS < 8, not able to obey verbal commands after sustained ROSC)	• Need for veno-arterial extracorporeal circulation before ROSC
• Patient affiliated with a social security system (If applicable)	• One of the following signs at echocardiography at hospital admission: - Acute core pulmonale, defined by right ventricular enlargement with interventricular septal deviation, associated with a Tricuspid Annular Plane Systolic Excursion (TAPSE) < 12 mm and need for vasopressor agents - Time-velocity integral of subaortic flow < 10 m/s
• Consent of the member of patients’ family or that of the trusted person if present and able to understand; otherwise certificate of emergency inclusion in compliance with applicable regulations.	
• Vent2Cool must be connected to a standard cuffed ETT of 7.0 mm to 9.0 mm internal diameter for the procedure. For 7.0 mm ETT, the IBW setting should not exceed 75 kg. For ETTs of 7.5 to 9.0 mm, the full range of the IBW setting (i.e. 40 to 93 kg) can be applied.	
	• Wrong positioning or damage of the endotracheal tube.
	• Women under 50 years old (childbearing age) or for women of > 50 years old, a positive pregnancy test (urinary) in case of pregnancy suspicion by the investigator. Possible breastfeeding during the study.
	• Suspicion of intracranial bleeding

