### Study intervention and target temperature management

Overall study design is illustrated by Fig. 1. After admission to the ICU and putative etiological treatment, if required, eligible patients could be included for URTH induction by Vent2Cool. Patients will be sedated and paralyzed with atracuronium and monitoring of muscle paralysis is recommended whenever possible. The maintenance of sedation and muscle paralysis after the Ven2Cool procedure will be left to the discretion of the physicians. Surface cooling device, that will be necessary to maintain hypothermia after induction by Ven2Cool, will be pre-positioned in order to avoid mobilization immediately after this procedure. However, the surface cooling system will not be active at this stage and until the end of the Vent2Cool procedure.

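### The primary endpoint does not require the target temperature to be reached while Vent2Cool is running, so one patient can be both a primary success and an induction failure

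*Protocol article*

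**What the plan says.** In the protocol article, Primary and secondary endpoints, success of the procedure has two parts. The temperature part is "defined as the ability to reach a body core temperature (bladder recommended) of 33.0 ± 0.5 °C". The ventilation part is "and a safe return to conventional mechanical ventilation within less than one hour after Vent2Cool start". The clock is fixed: "Start of the Vent2Cool procedure is defined as the opening of the Vent2Cool patient connector valve". The abstract gives the same two parts and also sets no order between them.

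Four other places bear on this:

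- **Table 1 (safety endpoints)** lists "Early termination of the Vent2Cool procedure before reaching a core target temperature below 33 ± 0.5 °C (failure of cooling induction").
- **Study intervention and target temperature management** says of the pre-positioned pads that "the surface cooling system will not be active at this stage and until the end of the Vent2Cool procedure". After return to gas ventilation they hold the patient at the same 33.0 ± 0.5 °C for 24 h. The same section lets the investigator stop at any time for safety, and states only as an expectation that the procedure ends after 33.0 °C is reached.
- **Table 2** records core temperature each minute for 60 min from the start, whether or not Vent2Cool is still running. It uses 33.5 °C as the limit for cooling rate and time to target.
- **Table 3** excludes "Temperature at admission < 34.0" °C. No temperature condition is stated for the moment of valve opening.

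**The concern.** The primary objective (Trial objectives) is to show what the Vent2Cool system itself can do. The endpoint as worded asks a looser question: was the patient in the band, and back on gas ventilation, at some time in the first hour? These differ for two kinds of patient:

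1. Vent2Cool is stopped above 33.5 °C, and the pads do the rest before minute 60.
2. Core temperature is already in the band when the valve opens.

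In a single-arm trial no control group offsets credit given to a second cooling device or to a low starting temperature. The first kind can include patients stopped for a safety reason, whom a first-in-human study should classify without doubt.

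The Table 1 limit adds to the problem. A value below 33 ± 0.5 °C is not one threshold: it can be read as below 32.5, 33.0 or 33.5 °C. A patient stopped at 33.3 °C is inside the primary band, yet is an induction failure under two of these three readings.

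**Working it through.** **1. The plan's own figure.** Sample size and statistical analysis gives 19/24 = 79.2%, 95% CI 59.5% to 90.8%, by Wilson's method. The limits are [p + z²/2n ± z·√(p(1−p)/n + z²/4n²)] / (1 + z²/n). With p = 19/24 = 0.7917, n = 24 and z = 1.96:

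- z²/n = 0.1601, so the denominator is 1.1601.
- Centre = (0.7917 + 0.0800)/1.1601 = 0.7514.
- Half-width = 1.96 × √(0.00687 + 0.00167)/1.1601 = 0.1561.
- Interval = 59.5% to 90.8%, which reproduces the stated figure.

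**2. Can one patient be in both classes?** Suppose Vent2Cool is stopped at minute 20 with core temperature above 33.5 °C and the patient is safely back on gas ventilation. Table 1 applies, because the procedure ended before target. The pads may now run. If a minute reading reaches 33.5 °C before minute 60, both parts of the primary definition are also met. Nothing in the article says which classification prevails.

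**3. How close to target must the stop be?** The article gives no surface-cooling rate, so I assume 1 °C/h (range 0.5 to 2), starting at once. The highest stop temperature that still reaches 33.5 °C by minute 60 is 33.5 + rate × (60 − stop minute)/60.

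| Stop at | 0.5 °C/h | 1 °C/h | 2 °C/h |
|---|---|---|---|
| 20 min | 33.83 | 34.17 | 34.83 |
| 30 min | 33.75 | 34.00 | 34.50 |

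The route is therefore open to a stop within roughly 0.25 to 1.3 °C of the limit.

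**4. In the band at the start.** A patient admitted at or above 34.0 °C is eligible. If core temperature has fallen to 33.5 °C (and not below 32.5 °C) by valve opening, the temperature part holds at minute 0. The Table 2 cooling rate, start temperature minus 33.5 °C over the time to 33.5 °C, then has a zero or negative numerator and no positive duration.

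**5. Effect on the rate.** Every patient who meets a definition tied to the procedure also meets the current one, so the difference has one direction. Each affected patient is worth 1/24 = 4.2 points. Starting from the planned 19:

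| Reclassified | Rate | Wilson 95% CI |
|---|---|---|
| 0 | 19/24 = 79.2% | 59.5 to 90.8 |
| 1 | 18/24 = 75.0% | 55.1 to 88.0 |
| 2 | 17/24 = 70.8% | 50.8 to 85.1 |
| 3 | 16/24 = 66.7% | 46.7 to 82.0 |

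The number reclassified is an assumption; the article gives none.

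**The case against.** The strongest reply is that the intent is clear. The endpoint is headed as success of the procedure, the objective names the device, the procedure is expected to end after 33.0 °C, and the pads are there to maintain temperature. The full protocol or the analysis plan, neither of which is shown, may already say that an induction failure is a primary failure. This stands as evidence of intent. It does not remove the conflict between two definitions that the article does state.

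The second reply is that few patients can be affected. At the rate above 15 °C/h quoted from animals in the abstract, the fall from 34.17 to 33.5 °C takes at most 0.67/15 × 60 = 2.7 min, so a stop inside that span is unlikely. A stop for safety may also fail the requirement of a safe return. Both points stand, although no human cooling rate is yet available. Drift before valve opening is likewise possible but unquantified. Start temperature, minute readings, procedure duration and early termination are all recorded, so an attentive reader could find these cases.

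A reader might be tempted to go further in four ways that the documents do not support:

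- **That 18/24 would miss a target.** The sample size rests on precision. The text says that 19 will have to succeed, but it states no decision rule and does not make 59.5% a threshold.
- **That overshoot should cancel success.** Table 1 already reports "Number and percentage of patients for whom the core temperature has reached a value lower than 30 or 32" °C as its own safety endpoint. Keeping it apart from a feasibility endpoint is a legitimate choice.
- **That safety is judged only up to minute 60.** The one-hour limit says when the return must occur. Table 1 separately follows related events to one hour after the end.
- **That a start at 34.0 °C is too easy.** That is a matter of eligibility and no fault in the definition.

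**Conclusion.** The point holds as a defect of wording in the primary endpoint. As written, a patient can be a primary success and an induction failure at once, and a patient already in the band at valve opening meets the temperature part without being cooled.

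The effect is 4.2 points per patient, always upward. The number of patients is unknown and probably small. The conclusion on wording rests on the article alone. The illustration of how near the target a stop must be rests on an assumed surface-cooling rate of 0.5 to 2 °C/h. The planned sample size and its interval are correct and unaffected.

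This is a cheap correction worth making before the results are analysed. It is not a flaw that undermines the trial, and nothing suggests that the plan means to credit Vent2Cool with cooling by another device.

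**What to change.** Make three changes to the endpoint wording, in the protocol and carried into the analysis plan:

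1. **Primary endpoint.** State that core temperature must first reach 33.5 °C or below after valve opening and before the Vent2Cool procedure ends (hence before surface cooling is activated), within 60 min, with the return to gas ventilation as now. Add that any induction failure under Table 1 is a primary failure.
2. **Table 1.** Replace the limit of below 33 ± 0.5 °C in the early-termination endpoint by the 33.5 °C limit that Table 2 already uses.
3. **Patients at or below 33.5 °C at valve opening.** Keep them in the denominator, do not credit them with cooling success, and report their number. Add a sensitivity analysis that excludes them.

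Leave overshoot below 32 or 30 °C and the adverse events as the separate safety endpoints already planned. These are rules for counting outcomes only; they say nothing on when treatment should be stopped.

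The cost is a wording amendment. Table 2 already provides the start temperature, the minute readings and the procedure duration, and the sample size stays at 24. The downside is that the reported success rate may be slightly lower. A patient whose reading crosses 33.5 °C just after valve closure would count as a failure, and the minute readings allow such cases to be described.
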